### Intervention

The SCTP is a competency-based, manualised training programme which evolved through review of the evidence, needs analysis and expressed requirements of care home staff.

The training course aims to increase the skills of care assistants and nursing staff in handling techniques (to facilitate movement) and to promote good positioning (to maintain functional posture) thus protecting body shape, avoiding choking, reducing pain and encouraging activity, so enabling residents to be as active and independent as they wish to be. The course is designed to be delivered to all those providing care (care assistants and nursing staff) rather than to be cascaded down to staff via the training of key workers. The course is practical in nature and emphasis is given to person centred care and the development of empathy towards residents.

SCTP will be delivered by expert physiotherapists (trainers) to staff in each of the five care homes randomised to the intervention arm. Two trainers are co-applicants who have developed the SCTP, and all four trainers are qualified physiotherapists who each have recognised training qualifications. Together they have optimised the training package for use within the trial and have undertaken detailed training and development work to ensure quality and consistency of delivery.

Course content is manualised to ensure consistency, but the emphasis will be adapted according to the particular needs of a home and individual staff members. This will be done in consultation with the care home management team after randomisation and before the first training session. The SCTP is generally presented in three 2.5-h sessions with a ratio of one trainer to a maximum of eight staff, but can be presented over two or one longer session(s) if this fits better with staff availability and training plans.

### Usual care

Control homes will continue to provide care as usual with no additional interventional input as a result of trial participation. No restrictions will be placed on homes undertaking additional training or development as part of their usual care. Data will be collected by researchers from care home managers at all 10 homes to describe usual care, any changes in practice over the duration of the trial, new procedures or care processes adopted by a home during the study period and staff turnover levels.

### Data collection

As the intervention will be delivered at the whole home level, it is important to assess the impact on the whole home. Thus data will be collected at the home level and from all care and nursing staff, as well as from and about participating residents. Data will be collected at baseline (before randomisation) and at three and six months post randomisation by blinded trial researchers who will visit each home at each time point. Maintenance of blinding will be monitored and reported by researchers as soon as they become aware of a care home’s allocation.

Personal details of participating residents will be held centrally, in accordance with the terms of consent or consultee agreement, to facilitate contact at follow-up time points. They will be held separately (both paper and electronic copies) to all outcome data.

A summary of assessments and outcome measures can be found in Table 1.

**Table 1 Tab1:** Summary and timing of assessments

Assessment	Method of completion	Timeline			
		Screening	Baseline	3 months	6 months
Screening, eligibility and consent					
Care home screening and eligibility	Researcher assessment / Researcher Interview (M)	X			
Resident screening and eligibility	Staff assessment with researcher support (S)	X			
Anonymous resident data: Physical Activity and Mobility in Residential Care Scale (PAM-RC) and Functional Ambulatory Classification (FAC)	Staff assessment with researcher support (S)	X		X	X
Trial consent (including process evaluation) (Resident (incl. personal/nominated consultee))	Self-completion (R) or Consultee (S, RF)		X		
Contact details (Resident (incl. personal/nominated consultee), staff informant	Researcher assessment (R, S, SI, RF)		X	(X)	(X)
Process evaluation consent	Self-completion (S)			X	X
Care home level data					
Care home demographics (including staff profile and training)	Researcher interview (M)		X	X	X
Home level resident profile	Researcher interview (M)		X	X	X
Significant events (D&V, temporary closure, CQC findings, change of manager/owner) and staff welfare	Researcher interview with manager / delegate (M)			X	X
Adverse events: total no. resident falls, hospitalisations and deaths	Researcher telephone interview with manager / delegate (M)		Collected monthly		
Staff measures (about the member of staff)					
Demographics	Self-completion (S)		X	X	X
Posture and movement questionnaire	Self-completion (S)		X	X	X
Kiersma-Chen Empathy Scale	Self-completion (S)		X	X	X
Person-Centred Care Assessment Tool (P-CAT)	Self-completion (S)		X	X	X
Resident measures (about the resident)					
Self-reported pain (Iowa Pain Thermometer)	Researcher interview / self-completion (R)		X	X	X
Perceived health (EQ-5D-5 L)	Researcher interview (R)		X	X	X
Six-item cognitive impairment text (6-CIT)	Researcher interview (R)		X	X	X
Posture observation tool	Researcher observation (R)		X	X	X
Staff-completed measures (about the resident)					
Activities of daily living (ADL) Barthel Index	Researcher interview (SI)		X	X	X
Perceived health (EQ-5D-5 L Proxy)	Researcher interview (SI)		X	X	X
Continuing Care Ability Measure (CCAM)	Researcher interview (SI)		X	X	X
PAM-RC	Researcher Interview (SI)		X	X	X
FAC	Researcher Interview (SI)		X	X	X
Resident information from care home records / staff					
Co-morbidities	Researcher collection from notes		X	X	X
Healthcare resource use	Researcher collection from notes		X	X	X
New therapies (individual) started since baseline	Researcher collection from notes			X	X
Pressure sores, falls, hospital admissions	Researcher collection from notes		X	X	X
Usual care and intervention data					
Observations of staff and resident interactions	Researcher observation		X	X	X
Usual care details (inc. new procedures or care processes)	Researcher interview (M)		X	X	X
Intervention fidelity and adherence (training, content, delivery, attendance)	Physiotherapist assessment (S)			X	X
Process evaluation data					
Views of intervention (inc. enablers and barriers)	Researcher interviews (S, R)			X	X

*M* care home manager, *R* resident, *S* care home staff, *SI* staff informant, *RF* relative/friend

#### Care home level data

At each time point, the care home manager or a nominated staff member will be asked to provide data to inform the staff and resident profile of the home. This will include: ownership (independent or part of a chain); number of beds in the home; full-time equivalent number of staff; engagement with local services (for example, community matron); and presence of specialist units (for example, dementia units). They will also be asked to provide details of their manual handling policy, staff training and any new initiatives they may be undertaking.

Anonymous home-level data will be collected on mortality, residents’ pressure areas, number and duration of hospital admissions, number of visits by health professionals, and falls for the six months before randomisation and for the duration of a home’s participation. For safety monitoring purposes whole-home falls, hospitalisations and mortality will also be collected via a researcher telephone call to the care home manager on a monthly basis post randomisation.

At baseline, as part of the screening process, and again at each follow-up time point, anonymous PAM-RC [20] and FAC [18] data will be collected for all residents to establish the activity and mobility profile of the home, and to establish the representativeness of the resident population taking part in the trial.

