### Care home randomisation

Following confirmation of eligibility and consent (or consultee agreement), and subsequent to baseline assessments with/about participating residents, at the level of the home and from individual staff members, care homes will be randomised on a 1:1 basis to receive SCTP or UC. Randomisation will be performed by the statistical team at the Clinical Trials Research Unit (CTRU), using block randomisation with randomly selected block sizes. Concealment of sequencing is ensured by the physically separate locations of the CTRU and the blinded study researchers.

Following randomisation, the CTRU statistical team will inform the unblinded members of the research team of the randomisation outcome, so that arrangements for training in the intervention can be made for those homes allocated SCTP. Unblinded members of the research team will be informed of the random allocation of the last two homes at the same time, to avoid predictability of care home allocation and selection bias in the recruitment of homes and/or residents. An unblinded member of the research team will inform the care home manager of the treatment allocation by telephone and email. This same member of the team will arrange follow-up visits with managers in an effort to keep researchers undertaking outcome assessment blind to allocation throughout the trial. This will ensure researcher follow-up visits are not arranged at the same time as intervention training sessions within the home and will allow reinforcement of the need to not divulge allocation details.

To ensure sufficient outcome data for evaluation at six months, despite initial assessment that there should be 12–15 eligible residents at a participating care home, a minimum of eight participating residents will be accepted for homes to proceed to randomisation.

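### As written, blinded researchers ask managers about staff training and new initiatives at 3 and 6 months, which makes unblinding likely in intervention homes

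*Protocol article*

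**What the plan says.** All places are in the protocol article.

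- **Data collection** sets the scope and the collector. On scope: "Thus data will be collected at the home level and from all care and nursing staff", alongside resident data. Collection takes place before randomisation and then "at three and six months post randomisation by blinded trial researchers who will visit each home at each time point".
- **Care home level data** sets the timing and content of the manager questions. The timing is "At each time point, the care home manager or a nominated staff member will be asked to provide data". The content includes "They will also be asked to provide details of their manual handling policy, staff training and any new initiatives they may be undertaking".
- **Table 1** lists "Care home demographics (including staff profile and training" and, in a separate row, usual care details with new procedures or care processes. Both are researcher interviews with the manager at baseline, 3 and 6 months.
- **Usual care** applies the second set of questions to all 10 homes, so SCTP homes are included. They cover changes in practice and "new procedures or care processes adopted by a home during the study period and staff turnover levels".
- **Care home randomisation** states the aim of keeping outcome assessors blind for the whole trial. An unblinded team member tells the manager the allocation and arranges the follow-up visits, which "will allow reinforcement of the need to not divulge allocation details".
- **Data collection** adds that researchers report when they learn a home's allocation.

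**The concern.** The instruction to managers and the questions put to them pull in opposite directions. The SCTP is a training course for care and nursing staff, so in an SCTP home a complete answer about staff training, new initiatives or new care processes names the allocated treatment. A manager who keeps to the instruction has to leave it out, and the record of training and usual care is then incomplete.

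Two things are at stake.

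1. **Detection bias.** Posture is scored by researcher observation, with a tool newly developed for this trial and meant for non-expert raters. Resident pain, EQ-5D-5L and 6CIT come from researcher-led interviews. A researcher who learns the allocation at 3 months cannot unlearn it before 6 months, the time point at which the arms are compared.
2. **A feasibility lesson.** The trial records whether blinding is maintained. If its own forms cause the unblinding, that record will understate how well blinding could be kept in a definitive trial.

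**Working it through.** The point is procedural and the plan attaches no figure to it, so there is nothing to reproduce. The statements are set side by side, followed by a sensitivity calculation for scale.

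**Step 1: who asks.** The Data collection section names home, staff and resident data together and gives the visits to blinded researchers. Nothing under Care home level data, Usual care or Table 1 moves the manager interview to an unblinded person. Where the article means unblinded staff, under Care home randomisation, it says so.

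**Step 2: what is asked, and when.** Staff training, new initiatives, manual handling policy and new care processes are asked about at 3 and 6 months, after allocation. The questions are not limited to training other than the SCTP.

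**Step 3: what an answer tells the researcher.**
- *SCTP home.* Homes whose staff had physiotherapy training in postural management and physical activity in the previous 12 months are excluded at entry. A new report of such training therefore points strongly to the SCTP arm.
- *Control home.* The Usual care section places no limit on additional training, and manual handling training is an entry requirement everywhere. Not hearing about the SCTP is a weaker clue, weaker still if SCTP managers withhold.

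**Step 4: whether the safeguards reach this interview.** Visit scheduling prevents a clash with training sessions. The reminder to managers asks for silence on the very thing the interview requests. Reporting of unblinding comes after the event. The staff booklets, which also ask about training, are returned in sealed envelopes; the manager interview has no such barrier.

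**Step 5: which outcomes are exposed.** Posture and the resident interviews are directly exposed. PAM-RC, the proposed primary outcome, is obtained by interviewing a staff informant. The SCTP is meant for all those providing care, so the informant can be expected to know the allocation whoever asks. Assessor blinding protects PAM-RC only in part.

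**Step 6: scale, under an assumed bias.** From the Sample size section: 5 homes per arm, 12 residents per home, 25% loss, ICC 0.03.
- Retained per home: m = 12 × 0.75 = 9.
- Design effect: 1 + (9 − 1) × 0.03 = 1.24.
- Effective number per arm: 5 × 9 / 1.24 = 36.3.
- Standard error of the difference in SD units: √(2 / 36.3) = 0.235.
- Critical value for two-sided 0.20 on 10 − 2 = 8 degrees of freedom: 1.397.
- Noncentrality: assumed bias / 0.235. The probability is the upper tail of the noncentral t beyond 1.397.

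| Assumed bias (SD), no true effect | Noncentrality | Chance that the 80% interval lies wholly on the SCTP side |
|---|---|---|
| 0 | 0 | 10% |
| 0.1 | 0.43 | 19% |
| 0.2 | 0.85 | 32% |
| 0.3 | 1.28 | 47% |

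The bias sizes are assumptions, as is applying this ICC to posture. The table shows sensitivity, not an expected effect.

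**The case against.** The strongest reply is that the article may be loosely worded rather than the design wrong. Table 1 also uses researcher interviews for views of the intervention, which a blinded person could not conduct, so researcher there need not always mean blinded assessor. The text on home-level data names no interviewer, and the article never says that one person does both the manager interview and the resident assessments. The interview wording is not shown and could exclude the SCTP. Managers are told not to divulge.

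Part of this stands: disclosure is likely, not certain. It does not remove the problem. The general sentence under Data collection covers home-level data without exception, and a manager who withholds leaves the training and usual-care record incomplete.

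Three stronger readings are tempting and not supported.

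- *That all ten homes are unblinded from the first follow-up, because not hearing of the SCTP is as informative as hearing of it.* Control homes may train staff too, and managers may keep silent.
- *That the false-positive rate of the planned test is inflated by a known amount.* The 20% significance test is planned for PAM-RC, whose informants can be expected to know the allocation anyway. For other outcomes the plan offers 80% intervals. No bias size can be drawn from the documents.
- *That the remaining visits can simply be changed.* Randomisation was projected to finish by the end of February 2018. Six months later is about the end of August, before publication on 24 September 2018, so few or no visits may remain.

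It is also fair that this is a feasibility trial not designed to judge effectiveness, and that loss of blinding is recorded.

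**Conclusion.** The point holds as an inconsistency in the procedures as written: the aim of blinding assessors throughout does not fit with giving blinded researchers a manager interview on training and new practices. Unblinding is likely in the five SCTP homes and less so, by inference, in the five control homes. Once it occurs at 3 months it carries to 6 months. The main exposure is posture and the resident interviews; the effect on PAM-RC is limited.

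This rests on reading the Data collection sentence as covering the manager interview, and on managers answering at least partly in full. Any size depends on an assumed bias: about 19% at 0.1 SD to 47% at 0.3 SD, against 10% with none. The point deserves correction but does not undermine the trial's feasibility aims.

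**What to change.** - Assign the 3- and 6-month manager items on staff training, new initiatives, manual handling policy and usual care to the unblinded team member who already contacts managers to arrange visits. Keep these items off the blinded assessors' forms and say so under Data collection and in Table 1. Asking them at the end of a 3-month visit would not be enough, because the researcher would still be unblinded for 6 months.
- For visits already completed, report unblinding by cause, with the manager interview as its own category, by arm and time point. Read the posture and resident-interview comparisons in that light.
- Write the separation into the definitive trial from the start.

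The cost is a wording change and some extra work for the unblinded team member: one set of manager questions per home at each follow-up, at most 10 × 2 = 20 in this trial. The article does not state that person's capacity. No data item is lost, and SCTP managers could then answer in full.

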#### Resident level data

Residents will complete the EuroQol 5-Dimension 5-Level (EQ-5D-5 L) [21, 22], the six-item Cognitive Impairment Test (6CIT) [23] and provide a self-reported pain assessment [24] via researcher interview, where they are able.

A purposely developed postural assessment tool will be completed via researcher observation of participating residents’ posture. This tool has been developed specifically for use in this trial after an extensive search revealed no appropriate existing tools to measure observed seated posture that would be suitable for use by non-expert staff (researchers who would not be able to physically examine the residents when observing them). Observation of the position of specific areas of the body (e.g. pelvis, thoracic spine) will occur at two time points separated by at least 1 h to allow assessment of any postural change or observation of sustained static seated position. Researchers will be trained in use of the tool by qualified physiotherapists.

The Activities of Daily Living (ADL) Barthel Index [25], Continuing Care Ability Measure (CCAM) [26] and EQ-5D-5 L proxy will be completed via researcher interview with each participating resident’s identified staff informant (a member of staff who knows the resident well).

Researchers will also collect information from care home notes for each recruited resident. This includes relevant co-morbidities, healthcare resource use, pressure sores, falls, NHS and social care contacts. In addition to collecting this data from care home notes, and in order to optimise data collection methods for the definitive trial, alternative data sources such as NHS Acute Trust records and NHS primary care notes systems will be explored. Participant information provision and consent includes these alternative methods of data collection. This will contribute to both the health economic analysis and safety profiles.

#### Staff data

All eligible care and nursing staff will be asked to complete a staff booklet which includes demographic data (e.g. role in the home, training undertaken), a purposely designed questionnaire to elicit their knowledge of posture and movement, the Kiersma-Chen Empathy Scale [27] and the Person-Centred Care Assessment Tool (P-CAT) [28]. These questionnaires have been chosen to reflect anticipated changes in knowledge, skills and attitude following SCTP training.

Staff will be asked to return completed questionnaire booklets in a sealed envelope, either directly by post to the research office or to a secure box located within the care home. Consent will be assumed by completion and return of the booklet.

#### Process evaluation

A mixed method approach will be adopted to explore the delivery and implementation of the SCTP.

Data regarding attendance, engagement, content and delivery of the SCTP will be provided by the trainers after every session in each of the five SCTP homes. This will be recorded on trial proformas which will allow reporting of adherence to the training content and schedule, as well as providing a summary of the level of staff understanding and engagement from the trainers’ perspective. Trainers will also have the opportunity to document any successes or difficulties, as well as deviations from the training plan, to allow for real-time reflection.

Observations of the delivery of a sample of the training will be conducted in each intervention home. Verbal consent for the researcher to observe the training will be obtained from trainers and care staff at the beginning of each session. If consent is not given by all members, the session will not be observed. The researcher will take brief summary notes during the training session and will develop these into expanded fieldwork notes as soon as possible after the session; this approach provides the opportunity to record data in more depth and detail than is possible during an observation [29]. Semi-structured interviews will be conducted with a maximum variation purposive sample [30] of participating care staff in the five intervention homes following the three- and six-month assessment points. The aim of this sampling approach is to explore how the intervention is perceived, understood and engaged with by different care home staff in the intervention sites at the different time points. The sample will vary in relation to staff roles (i.e. managers, qualified nurses, senior care staff and care assistants) and experience (i.e. length of time working in care homes). Interviews are anticipated to take approximately 45–60 min and will be conducted until the point of data saturation [31]. Interviews will cover topics such as: views of the training; what worked (success factors); what was less successful; knowledge; perspectives and attitudes towards residents’ posture and staff’s handling skills; and reflections on perceived or actual change in practice. After the final training session has been delivered, the trainers will also be asked to participate in a semi-structured interview that will explore their views and experiences of the training, elements that worked well and not so well, and their views on how care staff received the training. In order to obtain insight into residents’ views of their daily routines in the care homes and their experiences of any changes following the introduction of the intervention, informal conversational qualitative interviews will be undertaken with a purposive sample of residents who have participated in the trial and who have given informed consent as part of their agreement to trial participation. A sample of 8–12 residents in total, with differing physical and cognitive impairments drawn from the care homes participating in the process evaluation, will be sought. The interview format will be flexible in nature (in relation to the length of time the interview takes and the manner in which the researcher engages with the residents) in order to engage residents who may have differing communication and cognitive abilities. Interview topic guides will be devised drawing on the published literature relating to care home care practices and skills training and in consultation with the research team. Topic guides may be refined in light of ongoing data collection and analysis. Interviews will be conducted in a quiet private area and, with permission, audio-recorded. Informed consent specific to interview participation will be obtained from care staff and trainers.

To allow reporting of intervention enactment (using new skills in practice) in a future definitive trial, a trial-specific observational tool designed to record instances of care behaviours reflective of skills (that could have been) learned during SCTP training will be developed and tested in more than one site. A process consent approach will be used for these observations, with researchers explaining their purpose to all individuals present on each occasion observations take place. Verbal consent from staff, care home residents and visitors will be sought on each occasion observations are undertaken. Observations will only take place in public areas of the care homes and only if there is no objection from anyone within that area.

